#### Processes of care

Minimum care processes [H3] will be dichotomised as achievement of minimum care processes (at least 80% of all applicable processes of care administered) versus non-achievement of minimum care processes. A mixed effects logistic regression model will be used to assess between-condition differences on this binary variable. Time period, age at recruitment, injury type and severity (dichotomised mRS^16^ at baseline) will be controlled for as fixed effects in the model. Recruitment site and participant/individual will be included as random effects. In addition, time since injury and the interaction of time since injury with condition (control/intervention) will be included in the model. The interaction effect will be used to assess the between-group differences at 12 weeks post-injury [H3.1] and at 26 weeks post-injury [H3.2].

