**Fig. 1 Fig1:**
[figure not shown]
Implemented stepped wedge design

Participants were initially recruited within 4 weeks post-injury. This was amended during Period 1 to 6 weeks post-injury to enable recruitment of otherwise eligible patients who were only referred to the study immediately prior to the 4-week cut-off and for whom the recruitment process could not be organised within the short time frame. Outcome data were collected from participants and caregivers at 12 weeks and 26 weeks post-injury (as outlined in Table 1 below). Baseline assessments were predominantly conducted at the trial site at the time of recruitment. However, an amendment during Period 1 enabled recruitment in the community, to enable participants who were only referred to the study immediately prior to hospital discharge to be recruited. Participants were generally expected to have been discharged from the hospital sites prior to the 12-week and 26-week assessments. These assessments were therefore predominantly conducted off-site.

**Table 1 Tab1:** Schedule for collection of participant-level outcome measures

Data collection point (*time post-injury)*	Baseline (*0–6 weeks)*	1 (*12 weeks)*	2 (*26 weeks)*
Demographic data	X		
Type of injury (TBI/stroke)	X		
EuroQoL-5D-3L		X	X
mRS	X	X	X
FIM™	X	X	X
HADS	X	X	X
Participant satisfaction		X	X
Modified Caregiver Strain Index (administered to participant’s caregiver)		X	X

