#### System-level outcome measures

The health system-related outcomes recorded in this trial are:Minimum Processes of Care administered for each participant (including, e.g. use of interpreters, involvement of Aboriginal Liaison Officer, discharge plan involving family)Occasions of serviceResource utilisation using a purposefully designed questionnaire completed by each participant

These data are collected according to the schedule in Table 2 below:

**Table 2 Tab2:** Schedule for recording of system-level outcome measures

Data collection point (*time post-injury)*	Baseline (*0–6 weeks)*	1 (*12 weeks)*	2 (*26 weeks)*
Process of care indicators		X	X
Occasions of service		X	X
Resource utilisation		X	X

Resource utilisation will be used for the economic evaluation [16]

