### Data management

Data collected during the trial will be recorded and stored using the RedCap™ [31] electronic data capturing tool. Additional data on outpatient use of allied health services during the trial period will be obtained from the Western Australia Department of Health (WA DoH). Data on inpatient use of allied health services during the trial will be obtained from the Allied Health System (AHS) where possible and manual extraction from medical files when not. In addition, data on Minimum Processes of Care will be extracted manually from files at the participating hospital sites. These data will be stored in comma separated values (csv) files, which will be merged with the trial data from RedCap™ [31] during analysis. All data and scripts generated for analysis will be archived and stored at the lead institution (Edith Cowan University) for a period of 7 years. Access to this data will be controlled by the lead chief investigator.

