##### Minimum processes of care (MPC)

The trial protocol lists twelve processes or care, not all of which are applicable to all participants (e.g. not all participants will require an interpreter). The achievement of minimum processes of care (MPC) is defined as the achievement of at least 80% of all process of indicators that are applicable to a participant. The achievement of MPCs will be reported as a binary variable (achieved/not achieved) at 12 and 26 weeks post-injury. Frequencies and percentages by trial phase (control/intervention) will be reported.

Details of how these outcomes will be presented are outlined in Table 4 (12-week outcomes) and Table 5 (26-week outcomes) of Appendix.

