### Secondary statistical hypotheses

The secondary effectiveness hypotheses (H2–H5) yield the following statistical hypotheses:H2.1 Compared to usual care, implementation of the IP will result in increased occasions of service in the first 12 weeks post-injury.H2.2 Compared to usual care, implementation of the IP will result in increased occasions of service across the first 26 weeks post-injury.H3.1 Compared to usual care, implementation of the IP will result in an increased proportion of participants receiving at least the minimum processes of care in the first 12 weeks post-injury.H3.2 Compared to usual care, implementation of the IP will result in an increased proportion of participants receiving at least the minimum processes of care across the first 26 weeks post-injury.H4.1 Compared to usual care, implementation of the IP will result in an increased proportion of participants achieving independence as determined by mRS [18] at 12 weeks post-injury.H4.2 Compared to usual care, implementation of the IP will result in an increased proportion of participants achieving independence as determined by mRS [18] at 26 weeks post-injury.H4.3 Compared to usual care, implementation of the IP will result in increased FIM™ [19] at 12 weeks post-injury.H4.4 Compared to usual care, implementation of the IP will result in increased FIM™ [19] at 26 weeks post-injury.H5.1 Compared to usual care, implementation of the IP will result in lower scores on the Modified Caregiver Strain Index [20] at 12 weeks post-injury.H5.2 Compared to usual care, implementation of the IP will result in lower scores on the Modified Caregiver Strain Index [20] at 26 weeks post-injury.H5.3 Compared to usual care, implementation of the IP will result in lower anxiety as measured on the Hospital Anxiety and Depression Scale [21] at 12 weeks post-injury.H5.4 Compared to usual care, implementation of the IP will result in lower anxiety as measured on the Hospital Anxiety and Depression Scale [21] at 26 weeks post-injury.H5.5 Compared to usual care, implementation of the IP will result in lower depression as measured on the Hospital Anxiety and Depression Scale [21] at 12 weeks post-injury.H5.6 Compared to usual care, implementation of the IP will result in lower depression as measured on the Hospital Anxiety and Depression Scale [21] at 26 weeks post-injury.

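### Processes of care (H3): a participant random intercept on two nested yes/no values can give a degenerate or uninterpretable odds ratio; separate models per window should be the pre-specified analysis

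*SAP article*

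**What the plan says.** Under Secondary statistical hypotheses, H3.1 concerns the proportion of participants "receiving at least the minimum processes of care in the first 12 weeks post-injury" and H3.2 the proportion "receiving at least the minimum processes of care across the first 26 weeks post-injury". Both periods start at injury, so the second contains the first.

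The section Minimum processes of care (MPC) says: "The achievement of MPCs will be reported as a binary variable (achieved/not achieved) at 12 and 26 weeks post-injury". It also says: "The trial protocol lists twelve processes or care, not all of which are applicable to all participants". The System-level outcome measures section gives three examples: "use of interpreters, involvement of Aboriginal Liaison Officer, discharge plan involving family". Data management says that "data on Minimum Processes of Care will be extracted manually from files at the participating hospital sites". Study design adds: "Participants were generally expected to have been discharged from the hospital sites prior to the 12-week and 26-week assessments".

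The Processes of care analysis section dichotomises at 80% of applicable processes ("Minimum care processes [H3] will be dichotomised as achievement of minimum care processes (at least 80% of all applicable processes of care administered"). It fits a mixed logistic model with site and participant as random effects. The fixed effects are condition, time period, age, injury type, baseline severity, time since injury and the interaction of time since injury with condition. The interaction supplies the tests of H3.1 and H3.2.

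The section on the effect of the lower sample size expects that some models may not converge. It removes time period, mRS, injury severity, injury type and site, in that order. Only then does it allow separate models for 12 and 26 weeks.

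**The concern.** A participant random intercept suits repeated measurements that vary within a person. Here the second value is cumulative over a period that includes the first. The records come from the hospital, most participants should have left it before week 12, and the named examples look like inpatient or at-discharge acts. The two yes/no values may therefore agree for most participants.

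With two binary values per person and little within-person change, the likelihood favours a very large random-intercept variance. The fixed effects are on the participant-specific log-odds scale, so they grow with it. The analysis principles promise every treatment effect with a 95% confidence interval, so an odds ratio in the tens or thousands could be published as the pre-specified result. H3 is worded as a higher proportion of participants, and such a figure does not describe that.

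**Working it through.** The SAP gives no rate, effect size or agreement figure for H3, so there is no stated number to reproduce. Agreement between the two values is an assumption throughout, shown as a range.

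**Inputs.** 108 recruited (Recruitment rate section). Assumed: 54 per condition, no attrition, no site effect and no covariates.

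**Model.** logit P(Y_it = 1 | u_i) = η_gt + σu_i, with u_i standard normal, g the condition and t the timepoint. The population proportion is the average of expit(η + σu) over u.

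**Step 1: two-way change, proportions near one half.** Choose σ so that the average of 2·expit(σu)·[1 − expit(σu)] equals the share changing status. Then find the two values of η that give 40% and 57.1% (population odds ratio 2.0). The difference between them is the participant-specific log odds ratio.

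| Changing status | σ | Participant-specific OR |
|---|---|---|
| 30% | 2.0 | 3.2 |
| 20% | 3.6 | 5.6 |
| 15% | 5.0 | 10.0 |
| 10% | 7.8 | 32 |
| 5% | 15.9 | about 1,008 |

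**Step 2: maximum likelihood fits to explicit tables, change in both directions.** With 22/54 v 32/54 achieving at 12 weeks, the single-timepoint odds ratio is (32 × 32)/(22 × 22) = 2.12, z = 1.91.

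| Agreement | σ | OR at 12 weeks | z |
|---|---|---|---|
| 96% | 20.9 | about 18,000 | 1.41 |
| 93% | 10.3 | 136 | 1.63 |
| 89% | 7.0 | 30 | 1.71 |
| 85% | 4.9 | 11.6 | 1.78 |
| 78% | 3.0 | 5.1 | 1.83 |
| 70% | 2.0 | 3.4 | 1.86 |
| 63% | 1.3 | 2.7 | 1.87 |

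With 16/54 v 32/54, the single-timepoint odds ratio is 3.45 (z = 3.05). The model gives about 2,000 at 93% agreement, 45 at 85% and 6.7 at 70%, with z between 1.73 and 2.89 over the same range of agreement. In every case z falls; it does not rise.

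The numerical method also matters. These fits used dense quadrature. A Laplace approximation to the same likelihood gave 3.8 instead of 11.6 at 85% agreement, and about 13,400 instead of 136 at 93%.

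**Step 3: one-way change.** If achieved can never revert to not achieved, each condition has three patterns: never, late, and by week 12. As σ grows, the model reproduces any set of three proportions exactly. At any finite σ it wastes probability on the impossible reversal. The likelihood therefore has no maximum at finite σ. Take 28 never, 4 late and 22 by week 12 in control, and 18, 4 and 32 under intervention. The single-timepoint odds ratios are 2.12 at 12 weeks and (36 × 28)/(26 × 18) = 2.15 at 26 weeks.

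| σ held at | Log-likelihood | OR at 12 weeks |
|---|---|---|
| 2 | −116.12 | 3.65 |
| 8 | −97.86 | 51 |
| 16 | −95.86 | about 2,000 |
| 64 | −95.49 | above 10^12 |

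The upper limit (saturated log-likelihood) is −95.49. Tables with 0% to 30% changing one way showed the same absence of a finite estimate.

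**Step 4: the fallback.** The participant effect, which causes the problem, is not on the removal list. Time period, which separates intervention from calendar time in a stepped wedge, is removed first. Separate timepoint models come last, are optional, and choose the remaining effects by AIC. A fit that converges with an extreme variance triggers none of this.

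**The case against.** The premise rests partly on a list that is not shown. Three of twelve indicators are named, as examples only. Others could concern referral or post-discharge care, the coordinator works with participants to 26 weeks, and the set of applicable indicators may change over time. Early discharge is only a general expectation. This stands: near-duplication is a well-supported inference, and the consequences depend on agreement. At about 70% agreement with two-way change, the odds ratio is only about 1.6 to 1.9 times the single-timepoint value (3.4 v 2.12; 6.7 v 3.45).

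A participant-specific odds ratio is also properly larger than a population one when the variance is finite, because it is a different quantity. That is fair, but the SAP does not say which it intends, and its hypothesis is about proportions. Raw percentages by phase will be reported at both timepoints, which helps a reader spot an implausible figure but leaves the pre-specified estimate unusable.

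A reader might infer that the model is bound to fail, or that it would produce false-positive findings. The documents support neither: agreement is unknown, and z falls in the fits. A reader might also infer that H3.1 should be reduced to description. That is unnecessary, because separate models preserve it.

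**Conclusion.** The concern holds conditionally. The nesting is explicit; high agreement is likely but unproven. At about 85% agreement or more, a single-timepoint odds ratio of 2.12 becomes 11.6 or larger, and under one-way change there is no finite estimate. The size and interpretation of the effect, its confidence interval and the stability of the fit are at risk, not the false-positive rate. The existing fallback can reach a sound analysis, but only as an optional last step after the calendar-time adjustment has been dropped, and not when a degenerate fit converges. These figures assume a 54/54 split, no attrition, no site effect and no covariates. The outcome is secondary, so the point is worth correcting but does not affect the primary analysis.

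**What to change.** In the Processes of care section, make two separate mixed logistic models the pre-specified analysis: one for achievement by 12 weeks (H3.1) and one for achievement across 26 weeks (H3.2). Each has condition, time period, age, injury type and severity as fixed effects and site as random effect, with no participant effect and no time-since-injury terms. Keep both hypotheses. State that the H3.1 window is contained in the H3.2 window, so the two results are not independent confirmations.

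The cost is a change of SAP wording. The small downside is that there is no longer a joint test of the time-by-condition interaction.

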#### Stroke disability/injury severity

The score on the mRS [18] will be dichotomised as independent (mRS [18] 0–2) or dependent /dead (mRS [18] 3–6). A mixed effects logistic regression model will be used to assess between-condition differences on this binary variable. Time period, age at recruitment, injury type and severity (dichotomised mRS [18] at baseline) will be controlled for as fixed effects in the model. Recruitment site and participant/individual will be included as random effects. In addition, time since injury and the interaction of time since injury with condition (control/intervention) will be included in the model. The interaction effect will be used to assess the between-group differences at 12 weeks post-injury [H4.1] and at 26 weeks post-injury [H4.2].

#### Functional independence

A linear mixed effects regression model will be used to assess between-condition differences on the Functional Independence Measure (FIM™) [19]. Time period, age at recruitment, injury type and severity (dichotomised mRS [18] at baseline) will be controlled for as fixed effects in the model. Recruitment site and participant/individual will be included as random effects. In addition, time since injury and the interaction of time since injury with condition (control/intervention) will be included in the model. The interaction effect will be used to assess the between-group differences at 12 weeks post-injury [H4.3] and at 26 weeks post-injury [H4.4].

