### Assessments

Participants were assessed at three timepoints on the outcome measures outlined below—within 6 weeks of injury and at 12 and 26 weeks post-injury (see Table 1).

Demographic data, injury type and severity, functional independence measures and hospital anxiety and depression were recorded at the baseline assessment.

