## Statistical analysis plan

### Analysis principles and general considerations

All outcomes and analyses were prospectively characterised as primary or secondary.This is a superiority trial with intervention expected to yield superior outcomes, compared to control. However, all outcomes will be tested independently at the two-tailed 5% significance level. All estimates of treatment effects will be presented with 95% confidence intervalsNo formal adjustments will be undertaken to constrain the Type I error associated with planned secondary or exploratory analyses. The information provided by analyses is designed to supplement the evidence from the primary analyses; it will provide a more complete characterisation of the treatment effects.The analyses for all quantitative outcome measures will be conducted on an intention the treat (ITT) basis, i.e. all participants will be analysed in the trial phase (control or intervention) in which they were recruited, regardless of whether their treatment adhered to the trial protocol or not. The ITT strategy for this trial is based on the following principles:◦ All available outcome data are collected on all recruited participant◦ For the ITT analysis, the outcomes for each participant will be included in the data for the trial phase (control/intervention) in which the participant was recruited.◦ All available outcome data will be used in the primary analyses. The primary analyses will be reported without imputation of missing data. If the amount of missing data exceeds 10% at the primary endpoint, missing data will be imputed under the assumption that data is missing at random.◦ A sensitivity analysis including all randomised individuals will be conducted. The sensitivity analysis will consider alternative assumptions about data missing not at random (MNAR).For primary and secondary analyses, the treatment effects for the participant-level effectiveness outcomes will be adjusted for brain injury type (stroke or TBI) and severity of injury (mRS) [18] at baseline. In addition, age at recruitment, timepoint (time since injury) and time period (6-month block of time in which the participant is recruited to the step-wedge trial) will be included as fixed effects. Hospital site will be included as a random effect. Unadjusted analyses will be reported separately from these pre-specified analyses.All analyses will be conducted using the R Statistical Programming Language [32] after data collection is completed and the database is locked.

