### Outcome measures

#### Participant-level outcome measures

Participant-level outcome measures were measured at 12 weeks and 26 weeks post-injury, as outlined in the schedule in Table 1 (above). These include EuroQoL-5D-3L [17], mRS [18], FIM [19], HADS [21] and the Modified Caregiver Strain Index [20]. The mRS [18] score will be dichotomised into independent (0–2) or dependent / dead (3–6) and reported as a binary variable. Frequencies and percentages of the mRS [18] categories will be reported by trial phase (control/intervention). All other outcome measures will be treated as continuous; for these measures, the mean score will be reported together with the standard deviation.

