#### Anxiety and depression

Separate linear mixed effects regression model will be used to assess between-condition differences on anxiety and depressions scales of the HADS [21]. Time period, age at recruitment, injury type and severity (dichotomised mRS [18] at baseline) will be controlled for as fixed effects in the models. Recruitment site and participant/individual will be included as random effects. In addition, time since injury and the interaction of time since injury with condition (control/intervention) will be included in the models. The interaction effect will be used to assess the between-group differences at 12 weeks post-injury [H5.3] and at 26 weeks post-injury [H5.4].

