### Effect of lower sample size on statistical analysis plan

The final sample size of 108 was approximately one-third the estimated minimum required sample size of 312. As a result, one or more of our proposed mixed effects regression models (linear or logistic) may fail to converge. Nevertheless, we will attempt to fit the models as proposed in the first instance. If the model for an outcome measure fails to converge, we will approach the modelling of that outcome by removing effects from the model in the following order:Time periodmRS [18]Injury severityInjury typeSite

If the model for an outcome still fails to converge, the outcome may be modelled with separate models at each timepoint: 12 weeks or 26 weeks. In this case, time since injury and interaction between time since injury and condition (control/intervention) will be redundant. The other effects will be included in the model using a forward selection strategy to achieve the best model based on the Akaike Information Criterion (AIC). The assumptions for all statistical models will be assessed graphically using residual plots.

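### The FIM and HADS models leave out the baseline score that the trial collects, which loses precision and only partly corrects baseline differences between phases

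*SAP article*

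**What the plan says.** All references are to the SAP article.

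- **Baseline data exist.** Table 1 marks mRS, FIM and HADS at baseline, 12 and 26 weeks. The Assessments section confirms it: "Demographic data, injury type and severity, functional independence measures and hospital anxiety and depression were recorded at the baseline assessment". Baseline FIM and HADS are also to be reported in Table 3.
- **FIM model** (Functional independence): "Time period, age at recruitment, injury type and severity (dichotomised mRS [18] at baseline) will be controlled for as fixed effects in the model". Site and participant are random effects. Time since injury and its interaction with condition are added.
- **HADS models** (Anxiety and depression): "Time period, age at recruitment, injury type and severity (dichotomised mRS [18] at baseline) will be controlled for as fixed effects in the models", with the same random effects and interaction.
- **General rule** (Analysis principles and general considerations): participant-level treatment effects "will be adjusted for brain injury type (stroke or TBI) and severity of injury (mRS) [18] at baseline", together with age, timepoint and time period. The baseline value of the outcome is not mentioned.
- **Response times.** "Participant-level outcome measures were measured at 12 weeks and 26 weeks post-injury". The fallback for models that do not converge also names only these two: "the outcome may be modelled with separate models at each timepoint: 12 weeks or 26 weeks".
- **Removal order.** The same fallback drops time period first and mRS second.

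**The concern.** The baseline value of a repeated scale is often its best single predictor at follow-up. Here it has been collected and then left out of the models for hypotheses H4.3-H4.4 and H5.3-H5.6. The plan is also uneven: the mRS model adjusts for its own baseline in dichotomised form, while FIM and HADS do not adjust for theirs. The gap is widest for HADS, because mRS measures disability and says little directly about mood.

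Two things are at stake. One is precision, with 108 participants recruited against 312 planned (108/312 = 0.35). The other is balance. Four clusters were randomised, recruitment was uneven across sites and clusters, and entry conditions changed during the trial: proxy consent was unavailable from 2018 to 2020, the window moved from 4 to 6 weeks, and community recruitment was added. If a model fails to converge, the fallback can also remove mRS, the only baseline status measure it has.

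**Working it through.** **Is the baseline score really absent?** The two models and the general rule name their terms, and none is the baseline score. The participant random effect would bring it in only if baseline were a response row. The text does not expressly rule that out, but the outcome section and the fallback both name 12 and 26 weeks only. The natural reading is that baseline FIM and HADS are not used.

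**Plan's own figure.** There is none for this point. The 312 was derived for the VAS, and the plan gives no power, SD or correlation for FIM or HADS. What follows rests on assumptions.

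**Assumed inputs.**
- r, the marginal correlation of baseline with follow-up score: 0.3, 0.5, 0.7.
- q, the correlation of the underlying mRS with the baseline score: 0 to 0.8.
- Share dependent (mRS 3-6) at baseline: 50% or 70%.
- mRS predicts follow-up only through the baseline score. Age, injury type and time period are left out of the calculation.

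**Formula.** Variance factor VF = (1 - R² with baseline score) / (1 - R² with dichotomised mRS alone). Equivalent N = 108/VF. The SE changes by √VF. R² values come from simulation with 500,000 draws. As a check, a median split keeps about 0.798 of a correlation, so at r = 0.5 and q = 0.8 the R² for dichotomised mRS should be (0.798 × 0.8 × 0.5)² = 0.102. The simulation gave 0.101.

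| r | q = 0 | q = 0.8, half dependent |
|---|---|---|
| 0.3 | VF = 1 - 0.09 = 0.91; 108/0.91 = 119 | VF = 0.909/0.963 = 0.944; 108/0.944 = 114 |
| 0.5 | VF = 1 - 0.25 = 0.75; 108/0.75 = 144 | VF = 0.749/0.899 = 0.833; 108/0.833 = 130 |
| 0.7 | VF = 1 - 0.49 = 0.51; 108/0.51 = 212 | VF = 0.511/0.800 = 0.639; 108/0.639 = 169 |

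With 70% dependent, the factors lie within or very close to these ranges. Residual variance falls by 6-9%, 17-25% and 36-49%. The SE falls by about 3-5% (√0.944 = 0.972, √0.91 = 0.954), 9-13% (√0.833 = 0.913, √0.75 = 0.866) and 20-29% (√0.639 = 0.799, √0.51 = 0.714).

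**Balance.** Suppose a 0.3 SD baseline difference between conditions remains after the other terms, with no true effect and r = 0.5. The spurious effect is then:
- with no status covariate, 0.3 × 0.5 = 0.15 SD;
- with dichotomised mRS, about 0.15 SD at q = 0 to 0.2, 0.12-0.13 at q = 0.5, and 0.08-0.10 at q = 0.8;
- with the baseline score, about 0.

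Dichotomised mRS therefore removes little of the difference when it is weakly related to the score, as may be so for mood, and roughly 35-45% of it at q = 0.8.

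**The case against.** The strongest reply is that one prespecified covariate set for all outcomes is a defensible choice and contradicts nothing. These are secondary outcomes, which the plan treats as supplementary, and the size of any gain rests on correlations that the plan does not give. All of that stands. It limits the weight of the point but does not remove it: for any r above zero the direction is the same, and the data are already in hand.

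A second reply is that baseline is taken at 0-6 weeks, when staff at intervention-phase sites may already be trained and the coordinator may already have seen the participant. Adjustment could then remove some of the effect. This is a fair caveat, but it applies equally to the baseline mRS that every one of these models already uses.

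Some stronger readings are tempting but not supported:
- **That the models adjust only for dichotomised mRS and leave case-mix change uncorrected.** They also contain time period, age and injury type. Time period absorbs calendar changes common to all sites, which would include much of the proxy-consent hiatus. The correction is incomplete, not absent.
- **That most participants fall on one side of the mRS cut.** No baseline mRS distribution is shown.
- **That the plan contradicts itself on the form of mRS.** The general rule says "adjusted for brain injury type (stroke or TBI) and severity of injury (mRS) [18] at baseline" without a cut, and the model sections give the cut. That reads as a general statement made specific. Whether to enter the full score is a separate choice that these figures do not address.

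**Conclusion.** The point holds as a loss of efficiency and an incomplete correction in the FIM and HADS analyses. The omission is clear from the text; its size is not. At r = 0.3 the gain from adding the score is modest, and at 0.7 it is large. Every equivalent N ignores site-level variance and missing data, and the gain would be smaller if age and injury type already predict the score well. The balance figures depend on an assumed 0.3 SD difference and show direction, not an estimate for this trial.

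A reader might infer that the primary result is at risk. It is not: Table 1 schedules no baseline EuroQoL, so there is no baseline VAS to add and the primary analysis is untouched. The change is worth making because it is nearly free in a trial with about a third of its planned participants.

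**What to change.** - In Functional independence, add baseline FIM as a continuous covariate. In Anxiety and depression, add the baseline anxiety score to the anxiety model and the baseline depression score to the depression model.
- In the fallback under Effect of lower sample size on statistical analysis plan, state that this term is retained and is not removed ahead of the other covariates. Say the same for the separate-timepoint models, where the other terms are chosen by AIC.
- Handle missing baseline scores by simple covariate imputation, so that no participant drops out of a model for want of a baseline.

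The covariate form is preferable to entering baseline as a response with a common mean in both conditions, because that form assumes the equality between phases that is in doubt here.

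The cost is SAP wording and one more term per model, with no new data. The write-up should note that baseline scores at intervention-phase sites may not be strictly pre-exposure.
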